# Effectiveness of an intervention for improving drug prescription in primary care patients with multimorbidity and polypharmacy: study protocol of a cluster randomized clinical trial (Multi-PAP project)

**DOI:** 10.1186/s13012-017-0584-x

**Published:** 2017-04-27

## Abstract

**Background:**

Multimorbidity is associated with negative effects both on people’s health and on healthcare systems. A key problem linked to multimorbidity is polypharmacy, which in turn is associated with increased risk of partly preventable adverse effects, including mortality. The Ariadne principles describe a model of care based on a thorough assessment of diseases, treatments (and potential interactions), clinical status, context and preferences of patients with multimorbidity, with the aim of prioritizing and sharing realistic treatment goals that guide an individualized management. The aim of this study is to evaluate the effectiveness of a complex intervention that implements the Ariadne principles in a population of young-old patients with multimorbidity and polypharmacy. The intervention seeks to improve the appropriateness of prescribing in primary care (PC), as measured by the medication appropriateness index (MAI) score at 6 and 12 months, as compared with usual care.

**Methods/Design:**

Design: pragmatic cluster randomized clinical trial. Unit of randomization: family physician (FP). Unit of analysis: patient. Scope: PC health centres in three autonomous communities: Aragon, Madrid, and Andalusia (Spain). Population: patients aged 65–74 years with multimorbidity (≥3 chronic diseases) and polypharmacy (≥5 drugs prescribed in ≥3 months). Sample size: *n* = 400 (200 per study arm). Intervention: complex intervention based on the implementation of the Ariadne principles with two components: (1) FP training and (2) FP-patient interview. Outcomes: MAI score, health services use, quality of life (Euroqol 5D-5L), pharmacotherapy and adherence to treatment (Morisky-Green, Haynes-Sackett), and clinical and socio-demographic variables. Statistical analysis: primary outcome is the difference in MAI score between T0 and T1 and corresponding 95% confidence interval. Adjustment for confounding factors will be performed by multilevel analysis. All analyses will be carried out in accordance with the intention-to-treat principle.

**Discussion:**

It is essential to provide evidence concerning interventions on PC patients with polypharmacy and multimorbidity, conducted in the context of routine clinical practice, and involving young-old patients with significant potential for preventing negative health outcomes.

**Trial registration:**

Clinicaltrials.gov, NCT02866799

**Electronic supplementary material:**

The online version of this article (doi:10.1186/s13012-017-0584-x) contains supplementary material, which is available to authorized users.

## Background

Multimorbidity, the presence of various chronic diseases in the same individual, is the norm among the elderly population and very prevalent in the adult population in most Western European countries [1–3]. In Spain, the latest National Health Survey reports that individuals of over 75 years of age have an average of 3.2 chronic health problems, while the so-called young-old population (65–74 years) has an average of 2.8. Most studies define multimorbidity as the concurrent presence of two or more or three or more chronic diseases; the latter definition is more suitable for the identification of patients with complex health needs [4].

The potential negative health impacts of multimorbidity include reduced quality of life and functional capacity, inadequate use of health services, and increased complications and healthcare costs [5–7]. These effects are partly attributable to the current model of healthcare, which is essentially organized and designed to address diseases individually [8–10].

Although there is emerging evidence to support policy for the management of people with multimorbidity, the effectiveness of interventions is still uncertain [11], as is the case for clinical practice guidelines (CPGs) for patients with comorbidity [12]. The reality is that uncritical application of the recommendations of multiple CPGs for concurrent diseases in the same patient increases the likelihood of polypharmacy, defined by consensus as the simultaneous consumption of five or more drugs [13]. Family physicians (FP) have reported that this is a daily reality in primary care (PC) [14].

Polypharmacy implies an increased risk of medication-related problems such as interactions and adverse drug reactions, underuse of necessary treatments, low adherence, and partly preventable mortality, in particular in older patients [15]. Inappropriate choice of drugs with regard to age is another major problem, for which alternative (safer) approaches have been proposed that are equally or more effective [16].

Multiple approaches have been designed to measure and reduce inappropriate prescribing [17]. Explicit measures assess prescriptions according to predefined criteria related to the properties of the drugs concerned (e.g. Beers [18] and STOPP/START criteria [19]). However, these criteria may fall short in patients with multiple diseases and (interacting) treatments [20]. Therefore, implicit measures are applied to determine the level of appropriateness of prescribing. Based on the clinical judgment of the rater, implicit measures take into account the health status of the individual patient. The implicit method that is most accepted and validated, both internationally and in Spain, is the medication appropriateness index (MAI) [21, 22].

Evidence supporting the effectiveness of interventions to improve outcomes in patients with multimorbidity remains scarce [8, 23]. The Cochrane systematic review by Smith et al. [24] concluded that drug prescribing and adherence tend to improve when interventions target risk factors of multimorbidity and when they focus on key issues or specific functional difficulties affecting patients. Another Cochrane systematic review [25] evaluating the effectiveness of interventions aimed at minimizing the negative effects of polypharmacy concluded that, despite an overall improvement in prescribing by physicians, the effect on other clinical variables such as hospital admissions and quality of life is unclear. For this reason, the authors emphasized the need to incorporate into clinical trial outcome variables of relevance both for clinicians and patients and to evaluate intervention costs.

Various care programmes have been implemented in Spain to address polypharmacy in elderly patients (>75 years) by means of a systematic medication review in PC, and this strategy is supported by some evidence [26]. However, patients over 75 years of age constitute only part of the population with multimorbidity. Furthermore, these strategies do not meet the requirements of patient-centred care where patient’s preferences are taken into consideration. Shared decision making between health professionals and patients is also thought to improve patient’s adherence [27].

The sharing of common and realistic treatment goals between physician and patient is essential to tackle multimorbidity in the PC context and is the cornerstone of the Ariadne principles [28]. The implementation of these principles is based on a thorough assessment of the diseases, treatments and potential treatment interactions, global clinical status, and context of the patient by the physician. This allows prioritization of patients’ health problems, taking into account their preferences and wishes and ensuring their individualized management and monitoring. Despite numerous studies demonstrating the effectiveness of shared decision making on health outcomes [29–31], the feasibility of implementation and the impact of the Ariadne principles in PC have not been assessed to date, although the potential benefit of implementing such a strategy in routine clinical practice has been recognized [32, 33].

### Objectives

#### Primary

The main objective is to evaluate the effectiveness of a complex PC intervention implementing the Ariadne principles on the improvement of medication appropriateness in the young-old population with polypharmacy and multimorbidity, as measured by the differences of the MAI score at 6 months (T1) to baseline, compared with usual care.

#### Secondary

To evaluate the effects of the complex intervention on medication appropriateness after 12 months (T2), as well as on the use of health services, patient quality of life, treatment adherence, and medication safety, as compared with usual care.To study the cost-utility ratio of the intervention as compared with that of usual care.

## Method/design

### Design

Pragmatic cluster randomized controlled clinical trial with 12 months of follow-up. The unit of randomization is the FP and the unit of analysis is the patient. A cost-utility study will be performed from the perspective of the funder with a time horizon of 1 year.

### Scope of study

The scope of the study is the primary care setting of the Spanish national health system.

### Study population

The study population includes patients aged 65 to 74 years with multimorbidity and polypharmacy, attending PC health centres in three autonomous communities (ACs) in Spain: Aragon, Madrid, and Andalusia.

#### FP selection criteria

Employed in current position for at least 1 year.Stable employment situation, with no intention of leaving their position during the course of the study.Agree to participate and provide written informed consent.

#### Patient selection criteria

Inclusion criteria:Age 65 to 74 years.Multimorbidity, defined as ≥3 chronic diseases as per O’Halloran [34].Polypharmacy, defined as ≥5 drugs prescribed over at least the 3 months prior to inclusion in the study.At least one visit to the FP in the past year.Agree to participate and provide written informed consent.
Exclusion criteria:Institutionalized patients.Life expectancy of less than 12 months, as determined by the FP.Mental and/or physical conditions considered by the FP to prevent fulfilment of study requirements.

### Sample size

The sample size was calculated under the hypothesis that the intervention would lead to a difference of at least 2 units in the change in MAI score at 6 months (T1 vs T0) (i.e. a clinically relevant difference) between study groups. Differences in MAI are assumed to be normally distributed in each intervention arm and the variances are assumed to be equal. According to previous studies, the standard deviation of the difference in MAI is 6 units [32–34]. Therefore, the study should be capable of detecting an effect size of 0.3 (2/6). Considering a power of 80% and assuming simple random sampling, the required sample size would be 286 patients (143 patients in the intervention group and 143 in the control group).

The effective sample size in this type of study design depends on the average size of the cluster and the degree of correlation between individuals in the cluster. Accordingly, it is necessary to adjust the calculated sample size in accordance with the design effect (DE). An average cluster size of 5 patients per FP and an intraclass correlation coefficient of 0.03 [35] produces the following (DE = 1 + (5 − 1) × 0.03 = 1.12) which gives a sample size, corrected for the DE, of 320 patients. Assuming a percentage of losses of 20%, the final sample size required is 400 patients (200 per group). Assuming that each FP will recruit 5 patients, 80 FPs (40 per group) will be required. In each AC, 133 patients will be recruited.

### Recruitment

Voluntary participation will be proposed to FPs working in PC health centres in each of the three ACs. Patients will be added to a randomly ordered list of potential participants provided that they fulfil the inclusion criteria. Strategies to improve protocol adherence of FP will be considered (e.g. individual follow-up of protocol’s achievements and recognition via e-mail, offer to participate as co-authors in scientific papers, certified training sessions).

Each FP will consecutively select 5 patients from this list. When a patient agrees to participate, the FP will provide them with detailed information about the study, confirm the inclusion/exclusion criteria, and obtain the patient’s written informed consent. If they do not agree to participate, data on the patient’s age, sex, and reason for nonparticipation will be collected (see Fig. 1).

**Fig. 1 Fig1:**
[figure not shown]
Flow diagram

### Randomization

The unit of randomization is the FP and the unit of analysis the patient. Randomization of the FP will be achieved using the treatment assignment module of the Epidat 4.1 program; the proposed intervention will be considered the treatment and usual care considered the control. To ensure an equal number of FPs in each group (intervention and control), the ‘balanced groups’ option will be selected.

Once all participating FPs have selected their patients and collected the corresponding baseline data, FP randomization will be performed centrally by the Unidad de Apoyo a la Investigación, Gerencia Asistencial de Atención Primaria in Madrid. Subsequently, each FP will receive the information on the study group to which they have been assigned, at which point all patients recruited by him or her will be included in that group.

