### Explanatory and adjustment variables

#### Patient (first level) variables

Socio-demographics: age, sex, nationality, AC of residence, marital status, socioeconomic status (monthly salary expressed as multiples of the minimum wage), family composition (number of people living at home), housing indicators, social support (Dukes-UNC-11 questionnaire adapted to Spanish [43]), profession, and social class [44].Morbidity: number and description of chronic diseases based on the International Classification of Diseases in PC (ICPC).Pharmacotherapeutic treatment plan: number and type of drugs prescribed, active ingredient, and dose of each drug.

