### Statistical analysis

All analyses will be carried out in accordance with the intention-to-treat principle, with significance set at *p* < 0.05.

Description of baseline characteristics (qualitative and quantitative variables) of patients and professionals for each arm of the study, with corresponding 95% confidence interval (95% CI). Description of patients that abandon the study, including patient characteristics and reasons for loss during follow-up.

Basal comparison between groups using statistical tests for independent samples (Student’s *t* test or chi-square test). Tests for related samples (ANOVA for repeated measures) will be used to analyse changes within groups and between visits.

Analysis of main effectiveness: between-group difference in T1-T0 MAI score, with corresponding 95% CI. Multilevel analysis will be used to adjust models. Difference in MAI score will be considered the dependent variable; baseline patient (first level) and FP (second level) variables and treatment arm will be considered fixed-effect independent variables; and grouping by FP will be considered a random factor. Missing data pertaining to professionals and/or patients will be addressed by replacing missing values with the most recent available or baseline data.

Analysis of secondary effectiveness (non-confirmatory): between-group difference in means or proportions of T2-T0 MAI score will be determined using the appropriate statistical tests and an explanatory model will be adjusted using the same methodology applied to the main outcome variable.

Estimated quality-adjusted life years (QALYs) gained at the population level, with corresponding 95% CI, as determined using parametric methods and bootstrap techniques. Given the 1-year time horizon, no discount rates will be applied.

Calculation of cost-utility ratio: this is an exploratory objective for which a specific design has not been applied. The cost-utility ratio will be estimated by dividing the total cost by the sum of the potential gains expressed in QALYs. A multivariate sensitivity analysis will be performed in which costs will oscillate within the range of uncertainty of a normal distribution. The benefits (QALYs) will also oscillate within the same range.

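### Minor, free improvement: allocate FPs within each autonomous community, since one overall allocation leaves the regional split between arms to chance

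*Protocol article*

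**What the plan says.** The Randomization section makes the FP the cluster: "The unit of randomization is the FP and the unit of analysis the patient". It names the software and the one restriction used, the balanced-groups option, and gives its purpose: "To ensure an equal number of FPs in each group (intervention and control". On timing it says: "Once all participating FPs have selected their patients and collected the corresponding baseline data, FP randomization will be performed centrally". No stratification, blocking or minimisation by autonomous community (AC) is named.

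The Sample size section gives the number of clusters, "Assuming that each FP will recruit 5 patients, 80 FPs (40 per group) will be required", and the regional plan, "In each AC, 133 patients will be recruited".

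Community reappears at the analysis stage. It is listed under the patient-level adjustment variables ("Socio-demographics: age, sex, nationality, AC of residence, marital status"), and the Statistical analysis section describes the multilevel model for the change in MAI in these terms: "baseline patient (first level) and FP (second level) variables and treatment arm will be considered fixed-effect independent variables".

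**The concern.** The design controls regional composition at recruitment and then gives up that control at allocation. Because there is a single allocation, run when the full list of FPs is already in hand, nothing practical stands in the way of balancing within community.

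If mean outcomes differ between communities, an uneven split adds variability to any comparison that does not adjust for community, and makes it harder to read. Three places are exposed:

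- the crude between-group difference in T1-T0 MAI;
- the comparisons of health-service use;
- the cost-utility ratio.

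The article states no regional adjustment for the last two.

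**Working it through.** **Inputs.** From Sample size: 80 FPs, 40 per arm, 5 patients per FP, MAI difference 2, SD 6, intraclass correlation 0.03, losses 20%, equal recruitment by community. From Statistical analysis: significance level 0.05, taken as two-sided. Assumed here: 27/27/26 FPs per community, the nearest whole-number split of 80.

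**The plan's own figure.** A two-sample t-test with difference 2, SD 6 and 143 per arm has power 80.2%, so 286 patients reproduces. Design effect 1 + 4 × 0.03 = 1.12; 286 × 1.12 = 320; 320 / 0.80 = 400; 400 / 5 = 80 FPs. The sample size is not in question.

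**One community with 27 FPs.** With 40 of 80 FPs drawn for intervention, the number drawn from this community is hypergeometric:

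- mean 27 × 40/80 = 13.5;
- variance 27 × 0.5 × 0.5 × (80 − 27)/(80 − 1) = 6.75 × 53/79 = 4.53, so SD 2.13;
- the range 9 to 18 holds about 98% of the probability;
- a split of 17 v 10 or worse has probability 15.5%; 18 v 9 or worse, 5.8%.

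**All three communities.** Exact enumeration of draws of 40 from 27/27/26 gives:

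| Largest difference between arms in any one community | Probability |
|---|---|
| 5 or more FPs | 57% |
| 6 or more FPs | 38% |
| 7 or more FPs (7 × 5 = 35 patients) | 29.5% |
| 8 or more FPs | 17% |
| 10 or more FPs | 5.7% |

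Allocating within community reduces the difference to 0 (26 FPs) or 1 (27 FPs).

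**What this does to the MAI estimate.** The documents give no regional difference in MAI change, so a range is assumed: one community's mean change differs from the other two by d = 1 or d = 2 units. The second value equals the whole target effect. For a community of 26 FPs with X allocated to intervention, the unadjusted difference shifts by d × (2X − 26)/40. X has variance 26 × 0.25 × 54/79 = 4.44, so SD 2.11.

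- d = 1: added SD = 2 × 2.11/40 = 0.105, variance 0.0111.
- d = 2: added SD = 2 × 0.105 = 0.211, variance 0.0444.

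The planned variance of the difference, with 160 per arm after losses, is 36 × 1.12 × 2/160 = 0.504 (SE 0.71). The added shares are:

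- d = 1: 0.0111/0.504 = 2.2%; the interval widens by √1.022, about 1%;
- d = 2: 0.0444/0.504 = 8.8%; the interval widens by √1.088, about 4%.

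This treats the SD of 6 and the intraclass correlation as describing variation within communities. If they already include regional variation, the true addition is smaller.

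**The case against.** The main objection is that the analysis already deals with region. Community of residence is a listed adjustment variable and baseline patient variables are fixed effects in the primary model. The same methodology is carried over to the 12-month MAI model. With 80 clusters, stratified allocation adds little once community is in the model. This stands, and it limits the point to a minor one. The outcomes left more exposed also carry less weight: the article labels secondary effectiveness non-confirmatory and cost-utility exploratory.

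Several stronger readings are tempting but are not supported:

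- **Confounding.** A reader might infer that the treatment effect would be biased by region. Under a valid central randomisation the imbalance is random: the estimator is not biased in expectation and the type I error is not inflated. The cost is precision and ease of interpretation.
- **Too few clusters.** Forty FPs per arm is not a small-cluster design in which simple balanced allocation is fragile.
- **Known regional differences.** Nothing in the article says that communities determine service use, costs or prescribing. The Discussion describes the primary care model as relatively homogeneous across the country. Any regional difference is therefore an assumption.
- **A faulty quota.** 133 × 3 = 399 might look like an inconsistency with 400, but 133 is 400/3 = 133.3 rounded. Nothing depends on it.

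It can also be said that a condensed article does not expressly exclude allocation within communities. That carries limited weight: the section names the software, the option, its purpose, the timing and the responsible unit, and describes one allocation balanced on totals.

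**Conclusion.** The point holds as a minor design improvement. As described, the allocation leaves regional balance to chance when it could be secured at no cost, and a difference of 7 or more FPs in at least one community has a probability of about 30%. The result rests on 80 FPs split about evenly across the three communities.

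The consequence is modest. On the assumption that one community differs by 1 to 2 MAI units, the crude T1-T0 difference carries about 2% to 9% extra variance, most of which the adjusted primary model should recover. For service use and cost-utility the size cannot be given, because the documents contain no regional figures. Neither the validity of the primary test nor the sample size is affected.

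**What to change.** Keep the single central randomisation after baseline collection and the same balanced-groups option, but run it separately within each of the three communities. State in the Randomization section that allocation is stratified by autonomous community, and keep community as a fixed effect in the primary model.

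Where a community has an odd number of FPs, the extra FP is assigned at random. With 27/27/26 the totals are then 40 v 40 or at worst 41 v 39 (14 + 14 + 13 = 41). Even numbers of FPs per community, such as 26/26/28 = 80, would avoid this.

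The cost is three runs of the allocation module instead of one. The plan stays at 400 patients and 80 FPs.
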